1

General  
information

**Protocol reference Id**

20\_198

**Study title**

Epidemiology of anticoagulants prescribing in non-valvular atrial fibrillation patients in England: a cohort study exploring disease incidence and anticoagulants prescribing trends, comparing clinical outcomes, and risk of recurrent bleeding events

**Research Area**

Disease Epidemiology

Pharmacoepidemiology

**Does this protocol describe an observational study using purely CPRD data?**

No

**Sponsor**

University of Manchester

**Funding source for the study****Is the funding source for the study the same as Chief Investigator's affiliation?**

Yes

**Funding source for the study**

University of Manchester

**Institution conducting the research****Is the institution conducting the research the same as Chief Investigator's affiliation?**

Yes

**Institution conducting the research**

University of Manchester

**Method to access the data****Indicate the method that will be used to access the data**

Institutional multi-study licence

**Is the institution the same as Chief Investigator's affiliation?**

Yes

**Institution name**

University of Manchester

**Extraction by CPRD****Will the dataset be extracted by CPRD**

No

**Multiple data delivery****This study requires multiple data extractions over its lifespan**

No

**Data processors**

**Primary care data**

CPRD GOLD

CPRD Aurum

**Do you require data linkages**

Yes

**Patient level data**

HES Admitted Patient Care

ONS Death Registration Data

**NCRAS data****Covid 19 linkages****Area level data****Do you require area level data?**

Yes

**Practice level (UK)**

Practice Level Index of Multiple Deprivation

**Patient level (England only)**

Patient Level Index of Multiple Deprivation

**Withheld concepts**

**Are withheld concepts required?**

No

**Linkage to a dataset not listed**

**Are you requesting a linkage to a dataset not listed?**

No

**Patient data privacy**

**Does any person named in this application already have access to any of these data in a patient identifiable form, or associated with an identifiable patient index?**

No

**Lay Summary**

Despite improvements in the assessment of the risks of stroke and bleeding in people with atrial fibrillation – a common type of irregular heartbeat, many people are still not optimally treated with anticoagulants (blood thinners to prevent blood-clotting). It is believed that this may be due to overestimating patient's bleeding risk during anticoagulation therapy. The consequences of lack of anticoagulation could put patients at higher-risk for stroke or venous thromboembolism (blood clot), which are associated with long-term disability and death. Using UK primary-care data and hospitalization records from the Clinical Practice Research Datalink, we will determine how commonly atrial fibrillation is diagnosed in England and how it is treated. We aim to evaluate the factors that influence under-prescribing of anticoagulants in patients with atrial fibrillation in general and in a sub-group of patients with cancer, and explore their stroke and bleeding risk and concomitant therapy. We will use statistical methods to compare the risk of stroke, bleeding, or death among patients who received and did not anticoagulant therapy. We will separately examine patients who experienced severe bleeding due to anticoagulants, and whether they continued on anticoagulants after their bleeding episode. This will allow the identification of factors related to these prescribing decisions and how anticoagulants influence patients' clinical-outcomes. We will also assess and compare their risk for a stroke or another bleeding event using different risk-assessment tools. We anticipate that our findings will help in improving prescribing decisions of anticoagulant therapy in patients with atrial fibrillation at risk for stroke.

**Technical Summary****Background and Objective:**

Atrial fibrillation (AF) significantly increase the risk of ischemic stroke. The optimal use of oral anticoagulants (OACs) and control of stroke-related risk factors, is proven to substantially reduce stroke risk. However, some clinicians may not prescribe OACs to AF patients at-risk for stroke, as they believe that the risk of bleeding outweighs the benefit of anticoagulation. We aim to assess and compare the impact of prescribing anticoagulants by examining OACs prescribing in a cohort of non-valvular atrial fibrillation (NVAF) patients in England.

**Methods and Data analysis:**

The study comprises of three phases; first an epidemiological study that aims to delineate incidence of NVAF from the CPRD GOLD and Aurum databases between 2009 and 2019. Prescribing of OACs will be assessed for all patients with NVAF and in a sub-group with cancer diagnosis and relevant data will be extracted to identify potential predictors of OACs prescribing and further assessment using multivariable logistic-regression modelling. The second phase will be a comparative cohort study of incident NVAF patients who were classified as "OAC not prescribed" in phase one, by using a propensity score matching method to match each patient not prescribed OACs to up to 5 comparable patients treated with OACs. Then we aim to compare stroke, bleeding, and all-cause mortality associated with OACs prescribing versus no OACs. The third phase will focus on patients who developed major bleeding events in phase two while taking OACs. We aim to explore the variability of OACs prescribing after bleeding across patient groups and the different predictors for OACs resumption. We will explore the rate of bleeding reoccurrence, stroke, and mortality, and how they relate to OACs prescribing and timing of restarting OACs. We will assess and compare patients' risk for stroke and bleeding reoccurrence after the bleeding event using different risk-assessment scores.

## Outcomes to be measured

Throughout the different phases of this project we aim to explore the following outcomes:

- Phase 1 – The primary outcome is the prescription of OAC drugs including; vitamin K antagonists (VKAs) (acenocoumarol, phenindione or warfarin), or non-vitamin K oral anticoagulants (NOACs) (dabigatran, rivaroxaban, apixaban, or edoxaban).
- Phase 2 - The primary outcome is ischaemic stroke and other thromboembolic events, or the occurrence of major bleeding (MB) defined according to the International Society on Thrombosis and Haemostasis (ISTH) criteria as (1) clinically overt bleeding accompanied by a drop-in haemoglobin level of least 2 g/dl and/or (2) transfusion of at least 2 units of packed red cells, occurring at a critical site (i.e., intracranial, intraspinal, intraocular, pericardial, intra-articular, intramuscular, and retroperitoneal) and/or (3) fatal bleeding. Secondary outcomes will include clinically relevant non major bleeding (CRNMB) that did not satisfy the ISTH criteria and led to hospitalization, medical or surgical treatment, or led to discontinuation of OACs.
- Phase 3 – The primary outcomes include the reoccurrence of MB events or CRNMB for patients who did or did not continue on OACs, the rate of stroke and other thromboembolic events, cardiovascular related mortality, and all-cause mortality. The secondary outcome is the prescription of any OACs after the occurrence of the MB events. We aim to explore the timing of reinitiating OACs from the indexed MB event and whether patients have continued the same OAC before the index haemorrhage event, were switched to another OACs or received lone antiplatelet therapy.

All outcomes will be identified over the course of follow-up through the identification of corresponding Read/SNOWMED codes in patients' electronic health records. Hospitalization secondary to stroke or bleeding are to be identified through linkage to HES APC using the 10th revision of the International Classification of Diseases (ICD-10). ONS mortality data will be used to ascertain specific causes of death (i.e. bleeding related, cardiovascular, or all-cause death) according to ICD-10 codes.

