### Outcomes:

The primary outcome is the composite of ischaemic stroke and other thromboembolic events, or the occurrence of MB events defined according to the ISTH criteria (described in detail in Section D). Secondary outcomes will include CRNMB events that did not satisfy the ISTH criteria and led to hospitalization, medical or surgical treatment, or led to discontinuation of OACs. All outcomes will be identified over the course of follow-up through the identification of corresponding Read codes in patients’ records. For bleeding events since CPRD does not state the number of transfused blood units, any need for blood transfusion along with a Read code for bleeding will be classified as a MB event. Stroke or bleeding events will be identified through Read codes in patients primary care records and through linkage to inpatient HES ICD-10 codes in case of hospitalization secondary to stroke or bleeding. ONS mortality data will be used to ascertain specific causes of death (i.e. bleeding related, cardiovascular, or all-cause death) according

ICD-10 codes. All codes relevant to these outcomes are listed in Appendix 3.

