### 3. Phase 3 – Major bleeding events study cohort

**Exposures:**

The exposure of interest will be the occurrence of major bleeding events in the OACs exposed group from the phase two cohort. The exposure will be identified by at least one diagnostic code of a major bleeding event defined specifically according to the ISTH criteria (described in detail in Section D). Read/SNOWMED codes will be used to identify this exposure from patient's primary care electronic records, and hospitalization secondary to bleeding are to be identified through linkage to HES using ICD-10 codes (as listed in Appendix 3).

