**Covariates:**

- Patients' demographic information (age, gender, ethnicity, body mass index (BMI), geographic location (rural vs. urban), smoking status, alcohol consumption, Charlson comorbidity index for the severity of comorbidity (Appendix 3 and 4), electronic frailty index (eFI), and the index of multiple deprivation (IMD).
- Clinical covariates such as CHA2DS2-VASc, GARFIELD-AF, HAS-BLED, and HEMORR2HAGES risk assessment scores all at the time of the index haemorrhage event.

- Anatomic location of the index MB event will be identified and classified according to the critical site of bleeding (i.e., intraspinal, intracranial, intraocular, intra-articular, pericardial or other bleeding sites).

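### Major bleeding is defined with critical site only as a qualifier of transfusion, and the Phase 2 transfusion rule conflicts with that definition

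*Protocol*

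**What the plan says.** The detailed definition stands in the Protocol under Outcomes to be measured (Phase 2), which the later sections call Section D. It has three numbered routes:

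1. overt bleeding with a haemoglobin fall of 2 g/dl or more, with an and/or link to the next item
2. "transfusion of at least 2 units of packed red cells, occurring at a critical site", followed by a list of seven sites
3. fatal bleeding, joined by "and/or (3) fatal bleeding"

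A bleed that fails these is at most "clinically relevant non major bleeding (CRNMB) that did not satisfy the ISTH criteria and led to hospitalization" or to treatment or stopping of the anticoagulant. That category is a secondary outcome in Phase 2.

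Three later places use the definition:

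- **Phase 2, Outcomes.** Major bleeding (MB) is part of the primary composite, as "the occurrence of MB events defined according to the ISTH criteria (described in detail in Section D"). Because CPRD holds no unit counts, the section adds that "any need for blood transfusion along with a Read code for bleeding will be classified as a MB event".
- **Phase 3, Exposures.** Entry requires "at least one diagnostic code of a major bleeding event", and the sentence then refers back to Section D.
- **Phase 3, Covariates.** The index bleed is "classified according to the critical site of bleeding", with five named sites and a category for other sites. Intramuscular and retroperitoneal, both in the Section D list, are not named.

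**The concern.** In the definition, the joining word between alternatives appears only between the numbered items. Inside item 2 the site list follows transfusion after a comma, so site restricts transfusion and is not a route of its own. This has two consequences.

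First, a non-fatal bleed at a critical site that was not transfused, and for which no haemoglobin drop of 2 g/dl is on record, is not MB. An intracranial bleed is the obvious example. It leaves the Phase 2 primary composite, and its patient does not qualify for Phase 3. Yet the Study background motivates Phase 3 in part by the unsettled timing of restarting anticoagulants after intracranial haemorrhage.

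Second, the Phase 2 transfusion rule carries no site condition. A transfused bleed outside the listed sites is MB under that rule but not under item 2.

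The Study type section describes Phases 2 and 3 as hypothesis-testing. Two programmers working from this text could build different primary outcomes and different Phase 3 cohorts.

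**Working it through.** No figure in the Protocol depends on this definition. The sample size rests on stroke alone, so it is not affected. The check is therefore logical.

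**Inputs.** Four yes/no features of a coded bleed: H (haemoglobin drop of at least 2 g/dl on record), T (transfusion), S (critical site) and F (fatal). They give 2 × 2 × 2 × 2 = 16 patterns. T is a single indicator because unit counts are unavailable in CPRD.

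**Rules compared.** Each rule counts all 8 fatal patterns, so they differ only among the 8 non-fatal ones.

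| Rule | Formula | Non-fatal patterns counted | Total of 16 |
|---|---|---|---|
| A. Section D as written | H or (T and S) or F | 4 with H, plus 1 with T and S but no H = 5 | 13 |
| B. Section D plus the Phase 2 rule as a further sufficient condition | H or T or F | 4 with H, plus 2 with T but no H = 6 | 14 |
| C. Four separate criteria | H or T or S or F | all but the pattern with none = 7 | 15 |

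**The patterns that differ.**

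| Pattern (no H, not fatal) | A | B | C |
|---|---|---|---|
| Critical site, no transfusion | not MB | not MB | MB |
| Transfusion, non-critical site | not MB | MB | MB |

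Three points follow.

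- A and B disagree on the transfused non-critical-site bleed. That is a contradiction within the Phase 2 primary outcome. The stated reason, absent unit counts, explains dropping the number of units but not the site condition.
- The untransfused critical-site bleed is missed under both A and B, so the Phase 2 rule does not rescue it.
- Under B the site list has no effect at all: any bleed meeting T and S already meets T.

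**Alternative reading of the comma.** If the site phrase is taken to qualify items 1 and 2 together, the rule is (S and (H or T)) or F. It counts 8 + 3 = 11 patterns. That is narrower still, and site alone remains insufficient.

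**Where the missed bleed goes.** In Phase 2 it is non-major bleeding if it led to admission, treatment or stopping of the anticoagulant. As a first bleed it does not open Phase 3. As a recurrence within Phase 3 it still counts, because that outcome includes both major and clinically relevant non-major bleeds.

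**The case against.** The strongest reply is that this is a drafting ambiguity in one sentence, and that events will in practice be found through the Read, SNOMED and ICD-10 lists in Appendix 3. If those lists enter intracranial haemorrhage as MB, no such patient is lost. This stands as a limit on the practical effect. It does not clear the text, because such lists would then depart from the definition they are meant to implement.

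Three stronger readings are tempting, and the Protocol does not support them:

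- A reader might infer that the Phase 2 section makes transfusion a requirement. It states a sufficient condition, gives its reason, and keeps the reference to Section D. The conflict is confined to transfused bleeds at non-critical sites, where the rule adds events.
- A reader might take the Phase 3 entry sentence as a third, looser rule needing only one code. The sentence goes on to refer to Section D, so it inherits the definition and does not compete with it.
- A reader might infer from the Phase 3 site covariate that site alone was meant to qualify. A bleed that qualifies by any route has a location, and the list has a category for other sites. The only discrepancy shown is in the site lists.

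It is also fair to say that intracranial haemorrhage is only part of the case for Phase 3. The background opens that topic with major bleeding in general.

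**Conclusion.** The point holds on the Protocol's own wording and does not depend on the cited ISTH source. The definition as written leaves out two kinds of non-fatal bleed with no recorded haemoglobin drop: those at a critical site without transfusion, and those transfused at another site. The Phase 2 rule restores the second kind and so contradicts the definition. No section restores the first. The definition governs a component of the Phase 2 primary composite and the Phase 3 entry event, so it should be settled before the code lists are applied.

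The size is 2 of 16 logical patterns (15 − 13) against four separate criteria. These are patterns, not proportions of patients. A reader might want to state a percentage of MB events lost. That would need the share of bleeds at critical sites and the share of those with no other qualifying feature. The Protocol gives neither, and the answer also depends on Appendix 3, which is not shown. No percentage should be attached.

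**What to change.** - In Outcomes to be measured, list haemoglobin drop, transfusion, critical site and fatal bleeding as four separately numbered criteria, each sufficient alone.
- State there that, because unit counts are unavailable, any transfusion record with a bleeding code at any site meets the transfusion criterion, as Phase 2 already has it.
- State that a bleeding code at a listed critical site qualifies without transfusion.
- Use this one rule and one site list in Outcomes to be measured, Phase 2 Outcomes, Phase 3 Exposures and Phase 3 Covariates. Settle whether intramuscular and retroperitoneal belong in the Phase 3 list.
- Check the Appendix 3 code lists against the rule, so that each code can be traced to a criterion.

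The cost is Protocol wording and a code-list check. No new data or linkage is needed, and the sample size calculation is unchanged.

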### **Study design**

The first phase of this study will be a large population-based cohort study to identify incident cases of NVAf between January 1st, 2009 and 30th of June 2019; to determine the proportions of NVAf patients who have received a prescription for OACs or no treatment; to examine predictors of OACs prescribing. Given the described study aims and objectives, this study design will allow for a longitudinal analysis of incident NVAf cases and the subsequent timing of OACs prescribing with no comparator groups.

The second phase will be a comparative cohort study that aims to compare the clinical outcomes of NVAf based on their exposure status to anticoagulation therapy. Both patient groups will be identified from phase one and further divided into comparative groups of patients who have been prescribed OACs and patients with no anticoagulation therapy. The comparison will be undertaken after controlling for factors that could influence a patient's exposure to OACs and the outcomes to be explored, more details provided in section M.

Finally, the third phase of this study will be a separate analysis of the treatment group from phase two who have experienced major bleeding events. This study design is suitable for this phase as it will allow for a longitudinal analysis of NVAf patients from the indexed bleeding events and onward to evaluate the clinical outcomes (i.e. stroke, bleeding reoccurrence and mortality) related to OACs resumption or not and the timing of restarting OACs after the bleeding event, it will also allow for post-haemorrhage assessment of stroke and bleeding risk using different risk scores, and the identification of predictors for not resuming anticoagulation therapy.

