**Outcomes:**

The primary outcomes include the reoccurrence of MB events or CRNMB for patients who did or did not continue OACs, the composite of stroke and other thromboembolic events, bleeding or cardiovascular related mortality, and all-cause mortality. Secondary outcome is the prescription of any OACs after the occurrence of the major bleeding events (VKAs or NOACs). We also aim to explore the timing of reinitiating OACs from the indexed bleeding event until the date of OACs prescription, and whether patients have continued on the same OAC before the index haemorrhage event, were switched to another agent after bleeding have occurred (i.e. from warfarin to any NOACs or from any NOACs to warfarin) or received lone antiplatelet therapy.

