2. Phase 2 – Comparative study: For comparison of demographic variables and comorbidities among OACs treated and not treated individuals, independent sample t tests will be used for numeric variables, while Chi squared  $\chi^2$  tests or Fisher exact tests will be used for categorical variables. To control for imbalances in patient characteristics between cohorts, we will calculate an exposure-specific propensity score as the predicted probability of receiving OACs conditional upon individuals baseline covariate (as described in section M) using logistic regression models. Then we will consider applying propensity score matching methods to match each OACs unexposed controls to up to 5 NVAF OACs exposed cases using a calliper of 0.2 standard deviation (SD) of the propensity score logit. After matching, Cox regression will be used to compute hazard ratios (HRs) of the outcomes of interest, comparing exposure to OACs versus no OACs. Initially crude HRs will be obtained, then stratified by type of OACs (i.e., VKAs and NOACs) and adjusted for age, and other important covariates described in section N. In this phase immortal time bias would occur due to the definition of exposure, where in the time from AF diagnosis till receipt of OACs those in the “OACs prescribed group” cannot have the outcome by design, otherwise they would have been classified as non OAC users. To avoid the problem of immortal time bias, we will consider using time-varying exposures, where in a survival analysis, the time period previous to the index date of OACs initiation is reclassified as nonuser for those in the “OACs prescribed group”.

3. Phase 3 – Major bleeding events cohort: At first, we will use descriptive statistics to present the overall characteristics of this cohort who have experienced major bleeding events while taking OACs. After that patients will be divided to 2 groups one for the patients who resumed anticoagulation after the index major bleeding event and the other for the group who remained OACs free and will compare the patient characteristics between the two groups using Chi squared  $\chi^2$  tests, Fisher's exact tests, and analysis of variance, as appropriate. Survival (time-to-event) models will be constructed to compare the time between the indexed major bleeding to the earliest event of stroke, bleeding, or all-cause mortality considering if patients were restarted on OACs or not. In Cox models we will control for age, time to OACs resumption, CHA2DS2-VASc

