score and HAS-BLED score, Charlson comorbidity index, and eFI. In a secondary analysis, we will group patients who resumed OACs according to the type of anticoagulation drug used after the indexed bleeding events and compare the outcomes using Cox models in a similar manner. We will assess the proportional hazards assumption by examining Schoenfeld residuals and confirming that it is not violated. To identify variables independently associated with resuming

OACs after the indexed bleeding event multivariate logistic regression models will be used and fitted with the covariates described in section N. All the statistical analyses will be carried out using STATA (version 16).

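### Phase 3 models OAC restart after a major bleed as yes/no with no time window, so early death or short follow-up is coded as not restarting

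*Protocol*

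**What the plan says.** The protocol's Outcomes to be measured section, under Phase 3, says: "The secondary outcome is the prescription of any OACs after the occurrence of the MB events". The Phase 3 outcomes under Exposures, outcomes and covariates repeat this definition. Neither place sets a time window. The second adds that the authors will explore the "timing of reinitiating OACs from the indexed bleeding event until the date of OACs prescription".

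The Study design section gives as one purpose of Phase 3 "the identification of predictors for not resuming anticoagulation therapy". Specific aim 6 asks how resumption varies across patient groups.

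Under Data/statistical analysis, Phase 3, the cohort is split by what happens after the bleed: "patients will be divided to 2 groups one for the patients who resumed anticoagulation after the index major bleeding event". Everyone else falls into a second group, labelled as staying off OACs. No landmark or minimum observation time is given. For variables associated with resuming, the same section says: "OACs after the indexed bleeding event multivariate logistic regression models will be used and fitted with the covariates described in section N". The Plan for addressing confounding names multinomial logistic regression for the same question and does not list its outcome categories. Survival models are planned in Phase 3 only for stroke, bleeding or death after the index bleed, not for restart.

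The Limitations section notes that restarts made in hospital cannot be seen through the hospital linkage. It does not mention death or end of data before a restart.

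**The concern.** Whether a patient is ever seen to restart depends on two things: how readily prescribers restart, and how long the patient is alive and in the data. A yes/no outcome with no window mixes the two. NVAF cases accrue from January 2009 to 30 June 2019, so observation after a bleed can run from days to years.

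The Phase 3 covariates include age, the electronic frailty index, the Charlson index and bleed site. All can plausibly predict early death as well as prescribing. If they do, the logistic model will report mortality as prescribing behaviour, in a study whose stated purpose is to explain under-prescription. The results at stake are the restart part of Aim 6 and the predictors of not resuming.

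Restart timing raises a related problem. The interval ends at a prescription date, so it has no value for patients who never restart. If it is summarised among restarters alone, it is right-truncated by death and end of data.

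**Working it through.** The protocol gives no restart rate, no mortality after the bleed and no Phase 3 sample size, so there is no figure of its own to reproduce. The check asks what a yes/no analysis returns when the true effect on restart is nil. All rates below are assumptions.

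**1. Death competing with restart, one year of follow-up**

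Let h be a constant restart rate per year while alive, the same in two groups, and d the death rate per year, which differs. The probability of a restart within one year is

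F(h, d) = h/(h + d) × (1 − exp(−(h + d))),

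and the odds ratio is [F₂/(1 − F₂)] ÷ [F₁/(1 − F₁)].

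Worked case, h = 1.2:
- d = 0.22: 1.2/1.42 × (1 − exp(−1.42)) = 0.641
- d = 0.60: 1.2/1.80 × (1 − exp(−1.80)) = 0.556
- OR = (0.556/0.444) ÷ (0.641/0.359) = 0.70

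All combinations:

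| Restart rate h | d 0.22 v 0.60 | d 0.20 v 1.0 | d 0.10 v 0.40 |
|---|---|---|---|
| 0.8 | 0.75 | 0.58 | 0.78 |
| 1.2 | 0.70 | 0.52 | 0.73 |
| 2.0 | 0.61 | 0.41 | 0.62 |

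The death-rate ratios are 2.7, 5 and 4. The true restart rate ratio is 1.0 in every cell, yet the OR runs from 0.41 to 0.78.

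**2. Simulation with other assumptions**

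One million patients were simulated in two groups with the same restart hazard. Early deaths were uniform over months 0 to 3 and end of data was uniform over 0 to 60 months. Restart was scored yes/no with no window.

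| True median delay (months) | OR, 10% v 40% early death | OR, 20% v 50% early death |
|---|---|---|
| 2 | 0.31 | 0.39 |
| 6 | 0.37 | 0.41 |
| 12 | 0.45 | 0.46 |

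With no early death in either group the OR was 1.0, so the spurious effect comes from the difference in mortality.

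**3. Delay among observed restarters**

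In the same simulation with end of data only, the median delay among restarters was 1.9, 5.1 and 8.4 months against true medians of 2, 6 and 12. This shows the truncation mechanism alone. Unseen in-hospital restarts would make the first recorded prescription later than the true restart, and so lengthen recorded delays. The two act in opposite directions, and the protocol gives no figure for either.

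**The case against.** **Rules may sit elsewhere.** The study population section is one sentence, and censoring detail is commonly left to an SAP. That is fair as to detail. But the protocol itself chooses the outcome and names the model, and a logistic model cannot use a censoring rule. A restart window or minimum observation rule would help, and none is stated.

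**The model is not purely yes/no.** Multinomial regression implies more than two categories. They are unnamed, so death could be one of them. Even then, a model with no time axis cannot separate short from long follow-up.

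**The interval is only defined, not summarised.** This stands. The protocol gives the interval's start and end and says timing will be explored. It does not say that a median among restarters will be reported.

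**The proposed description keeps the contrast.** Cumulative incidence of restart with death competing also differs between the groups, and it is a legitimate descriptive target. This stands, and it is why death without restart must be shown beside it. With h = 1.2 and d = 0.20 versus 1.0, restart by one year is 0.646 versus 0.485. Death without restart, d/(h + d) × (1 − exp(−(h + d))), is 0.108 versus 0.404. Read together, the cause of the gap is visible.

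**Stronger readings a reader might infer:**
- *Restart delays will be biased short.* Not supported, because the Limitations section describes an effect in the opposite direction.
- *Aim 5 fails too.* Not supported. Its comparison of outcomes after the bleed rests on the Cox models and strata of restart time, not on the logistic predictor model.
- *Bleeds late in the data will show a specific false odds ratio against earlier bleeds.* No planned model estimates this, because bleed date is not a listed Phase 3 covariate.

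**Conclusion.** The concern holds for the predictors of restart. As written, patients who die or leave the data soon after the bleed count as not restarting, and the named models cannot correct for it. Characteristics linked to early death can then be misread as reasons not to restart. This reaches a secondary outcome, the restart part of Aim 6 and the search for predictors of not resuming.

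The direction is clear where a factor raises mortality and leaves the restart rate unchanged. The size is not known. The ORs above assume constant rates and a single unadjusted factor carrying a large mortality contrast. The planned model fits covariates jointly, so adjusted estimates for any one of them would differ. For restart delay, the truncation mechanism is real if only restarters are summarised, but the net direction is uncertain.

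**What to change.** In the Phase 3 part of Data/statistical analysis and in the Plan for addressing confounding, replace the logistic and multinomial models for restart with one agreed analysis:

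- Take survivors of the index bleed and model time from that bleed to the first OAC prescription.
- Use cause-specific Cox regression with death as a competing event, censoring at transfer-out or end of data.
- Describe restart and its type (same OAC, another OAC, lone antiplatelet) by cumulative incidence at fixed times, alongside the cumulative incidence of death without restart. Do not rely on the delay among restarters alone.
- Keep the existing caveat on unseen in-hospital restarts and apply it to the timing results.

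The cost is small. Hazard ratios and cumulative incidences replace odds ratios. The bleed, prescription and death dates are already needed for the planned Phase 3 analyses, and the named software can fit the models.
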